### Harms

A DSMC has been established. The DSMC is independent of the study team and consists of a psychiatrist (chair), neuropsychiatrist and biostatistician. The DSMC will monitor outcomes and be informed of serious AEs and withdrawals. The DSMC will advise study staff on (1) dose reduction, rechallenge or withdrawal in response to AEs, in consultation with the treating doctors; (2) withdrawal of participants due to escalation of agitation to an unmanageable level, resulting in physical aggression posing threat of harm to staff or property, in consultation with study psychiatrist; and (3) necessity of emergency unblinding in response to an AE. No further DSMC charter exists or is currently planned to be developed. The DSMC will not engage in interim analyses. Should a decision need to be made regarding early trial termination, this decision will be made jointly between study principal investigators and the DSMC.

Potential AEs will be monitored in the following ways:

1. Medical information—Weekly measures of weight, BP, HR and WC will be conducted by nursing staff at baseline, weekly throughout the treatment period and following emergence from PTA. Plans for the collection, laboratory evaluation and storage of blood samples are detailed in the provided (Additional file 1).

2. Blood tests—Blood tests assessing fasting lipids, fasting glucose, HBA1C and creatinine will occur at several time points: at baseline, upon the participant’s first score of 12 on the WPTAS (an early indicator of emergence from PTA), monthly throughout the treatment period and following emergence from PTA. Plans for the collection, laboratory evaluation and storage of blood samples are detailed in the provided Appendix: Biological Specimens.

3. The SAS [49]—This scale will be completed by the participant’s treating physiotherapist at baseline and weekly throughout the treatment period. The SAS is a rating scale for extrapyramidal system disturbance widely used to assess side effects related to antipsychotic drug use. It has well-established psychometric properties [49].

4. Adverse Events Questionnaire—This questionnaire will prompt reporting of AEs expected due to olanzapine use. This questionnaire will be completed weekly throughout the treatment period by the participant’s treating physician in partnership with study staff. Symptoms assessed will include respiratory issues, lethargy, nausea, vomiting, difficulty swallowing, constipation, urinary retention, dizziness and seizures. Information to be collected includes event description, start date, severity, relatedness to treatment, action with investigational product, expectedness, seriousness, outcome, end date and classification.

Clinically significant changes in these parameters will be recorded as AEs. Adverse events will be tabulated and tracked in a password-protected electronic file. All AEs will be followed to adequate resolution or stabilisation, including those that persist beyond the treatment period. If AEs continue beyond hospital discharge, follow-up will occur via telephone.

The DSMC will be informed of all serious AEs. A decision will be made by the treating doctor in consultation with a study psychiatrist and the DSMC as to whether withdrawal from the study, dose reduction or rechallenge is necessary.

Notification and reporting of AEs will be carried out according to the Australian regulatory, ethics committee and International Conference on Harmonisation Good Clinical Practice guidelines.

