## Background

The Australian Institute of Health and Welfare has reported a national traumatic brain injury (TBI) incidence of approximately 107 per 100,000 population per annum [1]. Productivity loss, economic costs and ongoing disability associated with TBI render this health condition a significant global public health concern [1–3]. Traumatic brain injury is frequently followed firstly by a period of coma and secondly by a period of post-traumatic amnesia (PTA). In moderate to severe TBI, PTA represents a period of recovery spanning days to months wherein the patient experiences generalised cognitive disturbance. This cognitive state is characterised by anterograde and retrograde amnesia, confusion, disorientation, attentional dysfunction, low arousal and poor awareness [4–7]. Patients in PTA often exhibit severe neurobehavioural symptoms [8–10]. Perhaps the most challenging of these is agitation, defined as an excess of behaviour involving restlessness, disinhibition and emotional lability [11–13]. When using a standardised measure of agitation, approximately one third of individuals exhibit agitation during the early stages of recovery from TBI [11, 14]. Agitation is problematic for patients, families and healthcare workers. Restlessness may lead to falls, and aggressive behaviour may result in self-harm, destruction of property and violence towards others [15, 16]. Agitation is associated with poorer rehabilitation engagement and longer hospital stays, and agitated patients reportedly exhibit poorer functional outcomes and less frequent return to private homes [8, 14, 17, 18].

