### Intervention, randomisation and allocation

Treatment will be administered by ward staff orally in capsule form. Study product may also be administered via nasogastric or percutaneous endoscopic gastrostomy (PEG) tube. Each active capsule will contain 5 mg olanzapine and 137.5 mg Flocel (filler). Placebo capsules will contain 142.5 mg Flocel (filler). Dosage will be flexible and titrated as follows: (1) one capsule at night (5 mg olanzapine or matching placebo per day); (2) one capsule in the morning, one capsule at night (10 mg olanzapine or matching placebo per day); (3) one capsule in the morning, two capsules at night (15 mg olanzapine or matching placebo per day); and (4) two capsules in the morning, two capsules at night (20 mg olanzapine or matching placebo per day). Dosage may be escalated every 3 to 4 days. The decision to escalate dose will be made based on whether ABS score reduces between dose escalation days, the clinical appropriateness of dose escalation and whether that participant’s ABS score is in the agitated range (ABS > 21). Should a participant’s ABS score fall below the agitated range (ABS < 22) whilst in PTA, gradual dose reduction to a minimum dose of one capsule at night (5 mg olanzapine or matching placebo per day) may occur in consultation with the participant’s treating doctor and study psychiatrist. All dosage changes for each participant will be reported. Specific data to determine dose range in this setting is not available. We therefore chose this dose range based on Australian regulatory approval of olanzapine dosages of 5–20 mg to treat other neuropsychiatric conditions, such as schizophrenia and bipolar I disorder [46].

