### Participant timeline

The participant timeline is displayed in Table 1 schedule of activities.

**Table 1 Tab1:** Schedule of activities

Study phase	Screening/consent	Baseline/randomisation	Treatment period (PTA)	Post-PTA	Discharge	Three-month follow-up
ACD/ MTDM identification	X					
Trial introduction	X					
MTDM consent	X					
Screening	X					
Participant consent				X		
Randomisation		X				
Demographics^a^		X		X		
Medical record^b^		X	X		X	
Medical information^c^		X	X	X		
Blood test(s)^d^		X	X	X		
WPTAS		X	X			
ABS		X	X	X	X	
Simpson-Angus Scale		X	X			
Administer treatment			X			
Treatment log			X			
AE monitoring^e^			X			
RAVLT				X		
SDMT				X		
SF-12				X	X	X
FIM				X	X	
MPAI-4						X
PDHSUQ						X

^a^Age, gender, years of education, marital status, pre-injury employment/study status, drug and alcohol history, psychiatric history

^b^One or more of date and cause of injury, Glasgow Coma Scale, PTA duration, imaging results, surgical intervention, other injuries, Injury Severity Score, therapy hours and number of sessions, special nursing care, medication details, number of patients on ward

^c^Weight, BP, HR, WC

^d^Assessing fasting lipids, fasting glucose, HBA1C, creatinine

^e^Respiratory issues, lethargy, nausea, vomiting, difficulty swallowing, constipation, urinary retention, dizziness, seizures

#### Baseline—day 0

Following eligibility confirmation and randomisation, the following information will be gathered from the participant’s medical record: baseline WPTAS and ABS, demographic information (age, gender, years of education, marital status, pre-injury employment/study status, drug and alcohol history and psychiatric history) and medical information (date and cause of injury, Glasgow Coma Scale score, PTA duration, imaging results, surgical intervention, other injuries, injury severity score, therapy hours, special nursing care and medication details). Pre-treatment measures of weight, blood pressure (BP), heart rate (HR) and waist circumference (WC) will be conducted by nursing staff. Blood tests assessing fasting lipids, fasting glucose, haemoglobin A1c (HBA1C) and creatinine will be conducted. The Simpson-Angus Scale (SAS; [49]) will be completed by the patient’s treating physiotherapist, in order to assess the presence of extrapyramidal symptoms.

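### The Adverse Events Questionnaire has no pre-dose completion although adverse events are defined as changes, so some pre-existing symptoms can enter the count or worsening can be misjudged (minor)

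*Protocol article*

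**What the plan says.** The Harms section of the protocol article lists four routes by which AEs are captured and then gives one definition for all of them: "Clinically significant changes in these parameters will be recorded as AEs".

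- **Adverse Events Questionnaire (item 4).** "This questionnaire will be completed weekly throughout the treatment period by the" treating physician, together with study staff. Its content is stated: "Symptoms assessed will include respiratory issues, lethargy, nausea, vomiting, difficulty swallowing, constipation, urinary retention, dizziness and seizures". For each event the form takes, among other things, a start date, severity and relatedness to treatment.
- **Table 1 (Participant timeline).** The AE monitoring row is marked under the treatment period only. Its footnote repeats the same nine symptoms: "Respiratory issues, lethargy, nausea, vomiting, difficulty swallowing, constipation, urinary retention, dizziness, seizures". The day 0 baseline text names no symptom questionnaire.
- **The other three sources.** The Simpson-Angus Scale is completed "at baseline and weekly throughout the treatment period". Weight, blood pressure, heart rate and waist circumference, and the blood tests, also have a baseline reading in both the Harms text and Table 1.

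Secondary outcome 1 compares the mean number of AEs between arms and names the questionnaire as one source. Statistical methods assigns that count to Poisson or negative binomial regression.

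**The concern.** A change needs a starting state. For the nine questionnaire symptoms the schedule collects none, although it does so for every other AE source. The schedule is stated twice and consistently, so this is a fixed feature of the plan and not a detail lost when the article was condensed.

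The document gives grounds to expect some of these symptoms before dosing:

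- **Lethargy (direct support).** Background describes post-traumatic amnesia (PTA), which is an entry condition, as involving "attentional dysfunction, low arousal and poor awareness".
- **Difficulty swallowing (inference).** "Study product may also be administered via nasogastric or percutaneous endoscopic gastrostomy (PEG) tube", which suggests that some participants cannot take capsules by mouth at entry. The text gives no reason for the provision.
- **Effects of earlier olanzapine (inference).** Screening lets study product start the evening after olanzapine of up to 10 mg per day, and during weaning from other agitation medication. The form is built around effects expected of olanzapine.

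At stake is the clarity of the AE comparison. A symptom carried in from the injury or from earlier medication can be recorded in either arm as if it arose on treatment, or a true worsening can be missed because nobody recorded how bad the symptom was before the first capsule.

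**Working it through.** **1. The plan's own figures.** The point disputes no number in the plan. The sample size reproduces: a two-sample t calculation at a standardised difference of 0.80, power 0.80 and two-sided alpha 0.05 gives 25.52, so 26 per group, and 26/(1 − 0.10) = 28.9, so 29. I use 26 per arm below.

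**2. Baseline by AE source (Table 1 and Harms).**

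| Source | Baseline | During treatment |
|---|---|---|
| Weight, BP, HR, WC | yes | weekly |
| Blood tests | yes | monthly, and at first WPTAS score of 12 |
| Simpson-Angus Scale | yes | weekly |
| Adverse Events Questionnaire | no | weekly |

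**3. Effect on the ratio.** The documents give no AE rates, so these inputs are assumptions: 1.0 on-treatment AE per placebo patient and 2.0 per olanzapine patient (true ratio 2.0). Two symptoms are each pre-existing in a proportion p of patients in both arms, and every one is miscounted, once. The added background is b = 2p per patient, so the observed ratio is (2.0 + 2p)/(1.0 + 2p).

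- p = 0.10: 2.2/1.2 = 1.83
- p = 0.20: 2.4/1.4 = 1.71
- p = 0.30: 2.6/1.6 = 1.63

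**4. Effect on the absolute difference.** (2.0 + b) − (1.0 + b) = 1.0 for every b. If the background is balanced, the expected difference does not move.

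**5. Precision of that difference.** Take on-treatment AEs as Poisson and the two symptoms as independent yes/no items, each arm gaining variance 2p(1 − p). Without background, SE = √((1.0 + 2.0)/26) = 0.340. With background, SE = √((3.0 + 4p(1 − p))/26):

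- p = 0.10: √(3.36/26) = 0.359, 6% larger
- p = 0.20: √(3.64/26) = 0.374, 10% larger
- p = 0.30: √(3.84/26) = 0.384, 13% larger

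**6. Power on the ratio scale, for orientation.** With a0 and a1 the observed means, n = 26 per arm and dispersion k, SE of the log ratio = √((1/a0 + k)/n + (1/a1 + k)/n) and power = Φ(ln(a1/a0)/SE − 1.96). At b = 0.5 (two symptoms at 25%), the ratio is 2.5/1.5 = 1.67. Power falls from 0.82 to 0.71 with k = 0 (Poisson) and from 0.61 to 0.44 with k = 0.5 (negative binomial). Both losses are on the high side, because the formula makes the background more variable than two yes/no items would be, most of all with k = 0.5.

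**The case against.** The strongest reply is that the text already guards against this. An unchanged symptom is not a change, so a physician who follows the definition does not record it. The form is completed by the treating physician with study staff, for inpatients whose records are at hand, and it takes a start date and relatedness. Events that began before the first dose can therefore often be identified. The rule on which events enter the count is ordinary content for the statistical analysis plan, which the article promises and which is not shown.

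Most of this stands. The absence of a counting rule from the article is not itself a fault, and several stronger readings that a reader might infer are not supported:

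- **That a drowsy, tube-fed patient would automatically generate two AEs in week 1.** This requires staff to record stable states as changes, against the stated definition.
- **That start dates are worthless because the patient is amnesic.** Dating does not rest on the patient's recall; physician, ward staff and chart are the source.
- **That all nine symptoms add background.** At 10% to 30% each this would add 0.9 to 2.7 AEs and bring the ratio to 2.9/1.9 = 1.53 down to 4.7/3.7 = 1.27. The documents support overlap directly for lethargy only, and by inference for swallowing and earlier olanzapine effects.
- **That the safety comparison is biased as defined.** Secondary outcome 1 is a difference in means, whose expectation is unchanged under balanced background.
- **That the AE count is the only protection against missing sedation.** Daily WPTAS scores, PTA duration, the RAVLT and SDMT, and length of stay also bear on it.

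What the reply does not remove is the missing severity. A start date can show that a symptom is old, but not whether it is now worse than before the first capsule, and later chart review can recover that only in part.

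**Conclusion.** The point holds in a limited form. The questionnaire is the one AE source without a baseline, under a definition that needs one. Some pre-existing symptoms can enter the count in both arms, and worsening can be misjudged. The likely consequence is a rate ratio nearer 1 and some loss of precision, without a shift in the expected absolute difference. Chance imbalance in background between arms of 26 to 29 remains possible.

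Under the assumptions above, the ratio falls from 2.0 to about 1.83 to 1.63, and the standard error of the difference grows by about 6% to 13%. These figures rest on assumed AE rates, an assumed prevalence for two symptoms, and every pre-existing symptom being miscounted. Raters who apply the definition and the start date would produce less dilution, possibly very little.

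Severity is minor. One component of one secondary safety outcome is affected, and the primary outcome is not.

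**What to change.** 1. Complete the same questionnaire once on day 0, before the first capsule, and add an X for AE monitoring under Baseline in Table 1.
2. In secondary outcome 1, count a questionnaire symptom as an AE only if it is new or worse in recorded severity than at baseline.
3. For participants already enrolled (Trial status gives 5), take the baseline state from the medical record while allocation is still blinded.

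The cost is one extra completion per participant of a nine-symptom form that staff already fill in weekly, plus one sentence in the outcome definition. Sample size, eligibility and treatment are unaffected.

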### Auditing

The investigators will permit study-related monitoring, institutional review board/institutional ethics committee review and regulatory inspection(s) and provide direct access to source data/documents.

### Data management, confidentiality and access

Participant case report forms and source documents will be stored securely at the Monash Epworth Rehabilitation Research Centre (MERRC). Data will be entered electronically at MERRC from original study materials into a password-protected file for analysis. Data transmitted electronically will be password protected.

To maintain anonymity, participants will be allocated a participant number. All raw and analysed data from tests and questionnaires will be labelled with that participant’s identifying number and will not contain information that could enable identification of individual participants. Any pre-existing identifying information contained within copies of original data collection materials (e.g. ABS, WPTAS, medical record) will be blacked out. A password-protected digital file containing each participant’s name, contact information and numerical identifier will be kept, separate from the study data. Only individuals authorised by the principal investigators will have access to study files. Data will be retained for 15 years from the date of publication of results.

All investigators will have access to study data. Data in de-identified electronic form may be made available to other researchers for the purpose of peer review. Data in this form may also be used for the purposes of further analysis by individuals authorised by the principal investigators.

### Dissemination policy

There are no publication restrictions associated with this study. Results will be published in international peer-reviewed journals and presented at academic conferences, regardless of the magnitude or direction of effect. Every attempt will be made to reduce to an absolute minimum the interval between the completion of data collection and the publication of study results. We expect to take approximately 6 months to compile the final results paper for an appropriate journal. Study results will also be published in the trial registry. Authorship criteria published by the International Committee of Medical Journal Editors [79] will be followed when submitting manuscripts for publication. The investigators do not intend to make the anonymised dataset or statistical code for generating results publicly available.

Upon the analysis of data, participants will be sent a letter informing them of study results, should they elect for this to occur in the Participant Information and Continuing Consent Form.

## Discussion

Agitated behaviour is distressing to patients, staff and families and is associated with poorer patient outcomes. Clinicians may employ environmental or pharmacological strategies when managing agitation in PTA patients. However, no quality evidence supports the use of any strategy for the management of agitation. Pharmacological intervention is common, and the use of antipsychotics amongst the most prevalent choice for treatment. Though preferred over their typical counterparts, the efficacy, safety and long-term outcomes associated with the use of atypical antipsychotics within this population are yet to be established. This trial aims to examine the efficacy of the atypical antipsychotic olanzapine in reducing agitation in PTA patients following TBI, over and above environmental management.

The major challenge associated with this trial has thus far been recruitment. This is thought to be the result of apprehension of MTDMs to consent to the patient’s participation in the trial, as well as difficulty fulfilling inclusion and exclusion criteria in a medically complex population. We will continue to explore possible avenues to mitigate these issues. One possible drawback of this trial is that the inclusion of olanzapine as rescue medication does not allow for a strict division between the treatment regime of placebo and olanzapine groups. However, this provision is expected to allow for the retention of highly agitated participants who would otherwise remain unrepresented in this sample, and those who would possibly be excluded following a single incident of escalation in agitation. This provision has also been made to protect the safety and promote the engagement of medical staff involved in the day-to-day care of these patients. The number of rescue doses administered to participants will be compared between groups, providing valuable insight into in whom and under what circumstances rescue medication was required.

The results of this trial will represent a major step forward in understanding the efficacy, safety and long-term outcomes associated with olanzapine use in this unique population. The results of this trial will inform the care of these patients, whose current standard of care is based predominantly on low-level evidence and physician’s clinical experience.

### Trial status

Recruitment for this project began in June 2019 and is expected to be completed by June 2022. The current recruitment status is 5. The protocol version at the time of submission is version 1.4, 21 October 2019.

## Data Availability

Not applicable

## Abbreviations

ABI: Acquired brain injury
ABS: Agitated Behaviour Scale
ACD: Advance Care Directive
AE: Adverse event
BP: Blood pressure
CONSORT: Consolidated Standards of Reporting Trials
DSMC: Data safety monitoring committee
FIM: Functional Independence Measure
HBA1C: Haemoglobin A1c
HR: Heart rate
MCS: Mental component summary
MERRC: Monash Epworth Rehabilitation Research Centre
MPAI-4: Mayo Portland Adaptability Inventory-4
MTDM: Medical Treatment Decision Maker
PCS: Physical component summary
PDHSUQ: Post-Discharge Health Service Utilisation Questionnaire
PEG: Percutaneous endoscopic gastrostomy
PTA: Post-traumatic amnesia
RAVLT: Rey Auditory Verbal Learning Test
SAS: Simpson-Angus Scale
SDMT: Symbol Digit Modalities Test
SF6D: Six-Dimensional Health State Short Form
SF-12: 12-Item Short Form Health Survey Version 2
TBI: Traumatic brain injury
WC: Waist circumference
WPTAS: Westmead Post Traumatic Amnesia Scale
